#### 3.2.3 Electroencephalography (EEG) and n-back paradigm

In this study, we use electroencephalography (EEG) to assess brain activity during a working memory paradigm. Like the fNIRS working memory paradigm, patients are administered an *n*-back task during EEG measurements; however, instead of letters, patients identify sequences of numbers and are instructed to click the space bar with their right hand when the stimulus appears. For 0-back, patients are instructed to hit the space bar when they see the number ‘**8**’. For 1-back and 2-back, whenever patients sees two numbers in a row or a pattern where the presented number matches the one shown before the previous number, they are expected to hit the spacebar as a correct response. EEG *n*-back was generated using a custom script created by PM, implemented in Matlab.

To measure real-time, continuous changes in brain activity, we use a wireless EMOTIV EPOC X headset (EMOTIV Inc., San Francisco, CA, USA) fit with 14 channels and 2 references, saline-based electrodes, and topography according to the international 10–20 system. The EPOC X headset has a sampling rate of 128 Hz, and bandwidth of 0.2–45 Hz with digital notch filters at 50 Hz and 60 Hz. EEG measurements are recorded with EMOTIV PRO software (EMOTIV Inc., San Francisco, CA, USA), outputting raw files that are used for further data processing, creating band-limited power spectra, averaged for each *n*- back block. Previous study has indicated changes in Beta power as being able to classify groups (AD vs. MCI vs. control) and subgroups within MCI that are likely to progress to dementia [72]. Hence, the addition of this methodology will aid in uncovering COVID-19 related changes within the neurovascular unit and better characterize the hemodynamic response measured by fNIRS. However, as COVID-19 is known as an endothelial disease [73] and data from CSF and autopsy studies indicate that neurons are likely not directly affected [74] even in olfactory impairments associated with the disease [75] we anticipate the EEG measure, in conjunction with our large battery of vascular measurements, to support that the changes in the hemodynamic response are primarily due to endothelial dysfunction.

EEG data processing and analysis will be implemented in Matlab 2022a (Mathworks, Natick, MA, USA) using custom scripts written by PM, implemented in a pipeline created by the EEGLAB toolbox [76]. Before analysis, data is cut into segments corresponding to the n-back blocks (0-back, 1-back, 2-back) and is low pass (0.5 Hz) and high pass (45 Hz) filtered. Channel locations will be defined according to the International 10–20 system. Components related to brain activity will be selected for further data analysis following wavelet-enhanced independent component analysis and multiple artefact rejection algorithm [77] aimed to attenuate extracerebral contributions to the recorded signal such as muscle activity and eye movements. Further, for each *n*-back segment, band-limited power in frequency domains of delta, theta, alpha, beta, and gamma will be generated through spectral analysis.

#### 3.2.4 Dynamic retinal vessel analysis (DVA)

The use of DVA is an emerging tool to study microvascular function in the retina, and importantly, can be used to study cerebromicrovascular pathology [78] because the retina shares embryologic origin with the central nervous system [79]. Before performing DVA, participants undergo extensive medical history screening (e.g., photosensitive epilepsy, history of glaucoma or glaucoma attack), are examined for visual acuity using a Snellen chart in a well-lit room, relevant ocular pathologies using a slit-lamp and IOP with an iCARE CI100 tonometer (Icare, Vantaa, Finland) and Goldman applanation tonometer. Chronically elevated IOP above 21 mmHg has significant risk for optic nerve damage [80] and because pupillary dilation may acutely increase IOP [81], patients are excluded from DVA measurement above an IOP of 21 mmHg. DVA is performed on the right eye after dilating the pupil with tropicamide (1% Tropicamide Ophthalmic Solution USP, AKORN, Lake Forest, IL), followed by a period of rest to ensure stable hemodynamic conditions. Using the Dynamic Vessel Analyzer (DVA, IMEDOS, Jena, Germany), the retinal arteriolar and venular diameters are evaluated [82]. Vessel segments of approximately 0.5 cm in length, located in the upper temporal quadrant at least 1 but not more than 3 papilla diameter distance from the edge of papilla, are assessed in the arteriolar and venular branches, while sites where two vessels are close to each other are avoided. The device allows for noninvasive and continuous assessment of retinal vessel diameters along a selected vessel segment. A 50 second (s) baseline recording is measured, then the first flickering stimulus (flickering light stimulation of 20 s in duration) is administered. Three flickering stimuli are administered throughout the duration of the test with 80 s of recording between stimuli. The mean of three consecutive examinations (20 s flickering stimuli and 80 s post-stimuli) are calculated for each participant [41] and used for analyses parameters. This methodology serves as a NVC measurement [41] and as a proxy for cerebromicrovascular function [79]. Hence, measured deficits in retinal arteriolar reactivity are reported to associate with cognitive impairment [78].

Data output from the retinal vessel analysis software generates continuous data for the entire 350 s measurement. With these data, we will assess relative maximal dilation percentage, relative maximal constriction percentage, time of maximal vessel dilation during flickering light stimulation, time of maximal vessel constriction, the area under the reaction curve during flickering light stimulation, and the area under the reaction curve after flickering light stimulation to determine vessel behavior following stimulus cessation.

#### 3.2.5 Assessment of peripheral macrovascular endothelial function using ultrasonography and flow-mediated dilation (FMD) protocol

To measure macrovascular endothelial function, we will use the gold standard flow-mediated dilation approach developed by Celermajer and colleagues [83] in the brachial artery (FMD) in accordance with the up-to-date tutorial presented by Harris et al. [84]. This method is endothelium dependent by opening of shear stress induced calcium channels activating endothelial nitric oxide synthase (eNOS), producing nitric oxide (NO), and allowing for diffusion of NO to the vascular smooth muscle to induce vasorelaxation. This mechanism has been validated in animal models, and in humans, showing an attenuation of the FMD response following the use of NO antagonists and an abolishment of the FMD response without an intact endothelium [85]. In addition, the use of FMD as a reliable non-invasive method to measure endothelial dependent function correlates with invasively assessed endothelial function [86]. A three lead ECG is placed on patients for continuous heart rate monitoring, allowing for removal of variability across the cardiac cycle during data analysis. Once attached, the study participants lay supine and rest for 20 minutes prior to the FMD measurement. Before baseline recording, patients’ blood pressure is measured for calculation of occlusion pressure (50 mmHg above measured systolic blood pressure, maximum 200 mHg) and a sphygmomanometer cuff is then placed below the antecubital fossa on the right forearm. The automatic cuff inflator (Hokanson E20 Rapid Cuff Inflator, Bellevue, WA, USA) is used to maintain pressure at 50 mmHg above the patients’ current systolic blood pressure during the occlusive phase. Brachial artery diameter is measured with a Doppler ultrasound system equipped with an 8–12 MHz transducer with pizo-electric crystals that transmits and receives the Doppler signal (Phillips Affinity 70, Philips North America Corporation, Cambridge MA, USA). After recording 60 s of stable baseline, FMD response is induced by release of the blood pressure cuff after 5 minutes of right forearm occlusion. After the cuff is deflated, changes in the diameter of the brachial artery are recorded for 3 minutes.

Brachial Analyzer for Research is used to calculate continuous change (15 frames per second) in brachial artery diameter across the duration of the measurement. Following calibration of the video recorded measurement, a region of interest (ROI) is selected for both baseline and post occlusion measures. ROI is selected based on signal clarity and intimal layer visibility. Following ROI selection, low boundary stiffness is selected for most precise measurement and borders determined by the BrachiAnalyzer software by automatic edge detection is accepted. Diameter measures are then calculated, and confidence threshold is set at 70%. Frames are reviewed by the operator to determine accuracy of automatic edge detection and, if needed, manual edge detection is performed to match the intimal layer. For accuracy of the baseline measurement (60 s), ten consecutive heart cycles are obtained for highest accuracy of baseline diameter. After review of all frames, auto-gating is conducted to detect R-peaks, removing influence of the cardiac cycle, resulting in end-diastolic diameter for the duration of the measurement. Processing is repeated for the post-occlusion video file. Data can then be exported, and FMD% can be used for statistical analysis [(Max diameter–average baseline diameter) / (average baseline diameter) * 100] [87].

#### 3.2.6 Assessment of peripheral microvascular endothelial function using laser speckle contrast imaging (LSCI) and flow-mediated dilation protocol

To measure endothelial function in skin microcirculation, we use the FMD approach coupled with LSCI. Decreased macro- and microvascular endothelial function is associated with cognitive dysfunction [87] and impairments in neurovascular coupling [42], leading to the hypothesis of generalized endothelial dysfunction impairing neurovascular coupling and leading to cognitive decline. This protocol is identical to the FMD approach with ultrasonography of the brachial artery; however, the blood pressure cuff is placed proximal to the antecubital fossa. Physiologic thermoregulation alters the diameter of blood vessels to either release or preserve heat [88]; therefore, to control for temperature, prior to and immediately after LSCI measurement we measure temperature of the regions of interest, middle fingernail bed and above first phalanx of middle finger, using a non-contact, laser-based thermometer (Thermoworks TW2, Thermoworks, American Fork, UT, USA). LSCI is equipped with a 785 nm laser (Perimed PSI system, Perimed, Järfälla, Sweden) and backscattering of light from movement of red blood cells through the microvasculature calculates microvascular perfusion. Through this methodology, we can measure continuous, real-time assessment of red blood cell movement in the skin microvasculature [89]. Experimental manipulations of endothelium dependent factors, such as NO, prostaglandins, adenosine and potassium, corroborates that this response is predominantly mediated by the microvascular endothelium, in conjunction with upstream mediated shear stress [90]. Similar to DVA, continuous measurement allows for multiple analyses to determine microvascular endothelial function.

Continuous measure of skin microvascular perfusion will be analyzed offline with the manufacturer’s software (PIMSoft, Perimed, Jӓrfӓlla, Sweden). We select two regions of interest, just proximal to the metacarpophalangeal joint of the middle finger, and the middle finger nailbed because this area has the highest capillary density. We will measure relative maximal dilation, time of maximal vessel dilation following release of the blood pressure cuff, and the area under the post-occlusive perfusion curve.

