### 2.9 Study variables

All variables included in the study are represented in **Table 1**, and separated based on level of measurement (continuous, ordinal, discrete, binary). Below, the variables are described for each specific aim, as mentioned in the *Study aims* section.

**Table 1 pone.0289508.t001:** Summary of variables for study aims.

Variable	Method of Measurement	Operational definition	Level of measurement
**NVC**	fNIRS	Change in relative HbO concentration in cortical small vessels during cognitive task	Continuous
**Band-limited power**	EEG	Amount of electrocortical activity in distinct frequency bands during cognitive task	Continuous
**Retinal arteriolar function**	DVA	Retinal arteriolar response to flickering light stimulus (NVC stimulus)	Continuous
**Microvascular endothelial function**	LSCI	Small vessel hand perfusion following the release of 5-minute occlusion	Continuous
**Macrovascular endothelial function**	FMD	Percent change in brachial artery diameter from baseline to release of 5-minute occlusion	Continuous
**Pro-inflammatory cytokine levels**	Magnetic bead-based multiplex assay	Quantified fluorescence intensity in pro-inflammatory cytokine levels	Continuous
**Endothelial dysfunction biomarkers**	Magnetic bead-based multiplex assay	Quantified fluorescence intensity in cardiovascular disease panel markers	Continuous
**Antioxidant capacity**	HORAC activity assay	Fluorescence decay curve: time until complete decay of fluorescent probe	Continuous
**Fluid intelligence**	NIH Toolbox	Individual and categorical T score based on cognitive test responses	Continuous
**Crystalized Intelligence**	NIH Toolbox	Individual and categorical T score based on cognitive test responses	Continuous
**Emotion Score**	NIH-Toolbox	Individual T-score based on normative population data	Continuous
***n*-back working memory performance**	n-back	Percentage of correct responses and reaction time during *n*-back blocks	Continuous
**Blood pressure**	AD instruments	Blood pressure recorded during visits	Continuous
**Time since SARS-CoV-2 Infection**	Demographic	Duration from COVID-19 diagnosis to Visit 1	Continuous
**Age**	Demographic	Age (in years) of participants at each visit	Discrete
**Fazekas scale**	MRI	WMH burden (0–3) periventricular and deep	Discrete
**MoCA**	Demographic	Montreal cognitive assessment score (0–30)	Discrete
**ACE score**	ACE questionnaire	Adverse childhood experience questionnaire, scored 1–10 with a score of 10 having high ACE	Discrete

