### 3.2 Physiological investigations

#### 3.2.1 Blood pressure measurement

Blood pressure (BP) is measured in accordance with the 2017 AHA/ACC Hypertension Guideline for Standard Measurement of BP [56]. Recordings are taken several times during each ~four-hour visit, before cognitive testing, before FMD, and before LSCI. Uncontrolled hypertension is known to cause deleterious effects to the endothelium and systemic vasculature [57]. Hence, patients with uncontrolled hypertension are excluded, in brief, due to known impairments of cerebral autoregulation [58], risk of cerebrovascular complications [59], and dysregulation of the macro- and microvasculature [60].

Systolic, diastolic, and mean arterial pressure will be calculated from patient blood pressure recordings and compared between groups (COVID-19+ and COVID-19-) to assess for differences, which may influence vascular physiological measurements.

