## 4. Statistical analysis

### 4.1 Cross-sectional data analysis

Upon testing for normality of continuous data, independent t-test or Mann-Whitney *U* Test will be used for group comparison (COVID+ vs COVID-) and Chi-square or Fisher’s exact test for group comparison of categorical variables. Effect size will be calculated for all within and between group analyses. For **primary outcome** analysis, testing whether COVID-19 impairs NVC responses in MCI patients, fNIRS data will be analyzed using a pipeline based on General Linear Model (GLM) approach created using the Brain AnalyzIR toolbox. At the first (subject) level, regression (β) coefficients characterize NVC response and will be estimated for channels of interest in the prefrontal cortex across all n-back blocks and chromophores (HbO and HbR). At the second (group) level the GLM treats COVID status as an independent categorical factor, while the n-back block as a repeated measures factor and yields corresponding *t*-contrasts comparing NVC response within and between groups. We will test whether demographic variables, COVID-19 variants, duration of COVID-19 and vaccination influences the primary outcome through linear regression. Moreover, we will create a multivariate model using β coefficients, generated from the fNIRS pipeline, to determine whether COVID-19 predicts impairment in NVC in MCI patients. Univariate analyses of factors that may contribute to NVC impairment (i.e., age, sex, baseline structural MRI abnormalities) will be conducted, and analyses with a p value of <0.2 will be included in the multivariate model. **Secondary outcome** measures (i.e., FMD, LSCI, EEG, DVA, NIH Toolbox, circulating factors) will be compared between groups. Additionally, we will determine whether history of COVID-19 contributes to impairment in functional cognitive measures (i.e., n-back, NIH Toolbox) by multiple and simple linear regression. For **exploratory analyses**, we will determine whether group (COVID+ vs COVID-) alters the relation between NVC and peripheral, cognitive, and structural measures through multiple regression. Correlations for these variables will be performed within groups to determine strength of relationship with NVC.

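### Skin temperature is recorded to control the LSCI perfusion measure, but its second site is described inconsistently and no named LSCI analysis can use it

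*Protocol article*

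**What the plan says.** Section 3.2.6 notes that thermoregulation changes vessel diameter and gives the reason for the thermometer reading: "therefore, to control for temperature, prior to and immediately after LSCI measurement we measure temperature of the regions of interest". The two sites are then listed: "we measure temperature of the regions of interest, middle fingernail bed and above first phalanx of middle finger".

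The following paragraph of 3.2.6 defines where perfusion is analysed: "We select two regions of interest, just proximal to the metacarpophalangeal joint of the middle finger, and the middle finger nailbed". Three LSCI parameters follow. "We will measure relative maximal dilation, time of maximal vessel dilation following release of the blood pressure cuff" covers two of them, and the third is the area under the post-occlusive perfusion curve.

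Section 2.9 introduces Table 1 with "All variables included in the study are represented in" that table. Its LSCI entry reads "Small vessel hand perfusion following the release of 5-minute occlusion". Skin temperature has no row, and it is not among the Aim 1 variables listed after the table.

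Section 2.8 makes LSCI a secondary outcome. Section 4.1 compares COVID-positive and COVID-negative patients on continuous measures by t-test or Mann-Whitney test. Section 4.2 uses 2-way ANOVA for continuous longitudinal data. Both sections mention LSCI only in a shared list of secondary measures to be compared, with no covariate.

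**The concern.** A nuisance variable is collected for a stated purpose, and the analysis as described cannot serve that purpose. There are two separate faults.

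First, the same section uses the term regions of interest for two lists that agree on the nail bed but not clearly on the other site. An operator following the text could point the thermometer at the finger while perfusion is read on the hand. The study is already under way (section 2.3), and a temperature that was not taken at the perfusion site cannot be recovered later.

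Second, nothing says how the reading exercises control. The article gives no covariate term, acceptance range, exclusion rule or room condition.

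LSCI is the only variable for peripheral microvascular endothelial function in Table 1, and it supports Aim 1. At stake are the precision of that comparison and, if the groups happened to differ in skin temperature, its validity.

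**Working it through.** The documents give no power, effect size or variance for LSCI, so there is no figure to reproduce. The check is a comparison of text, followed by an illustration on stated assumptions.

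**Sites (3.2.6)**

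| | Temperature reading | Perfusion region |
|---|---|---|
| First | middle fingernail bed | middle finger nail bed |
| Second | above the first phalanx, middle finger | just proximal to the metacarpophalangeal joint, middle finger |

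The first row agrees. In the second row, a reading taken over the first phalanx lies distal to the joint, while the perfusion region lies proximal to it. If above means proximal to the phalanx, the two coincide. The text allows both readings.

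**Route into the analysis**

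- Table 1 has no row for skin temperature, although it does have one for blood pressure, another condition of measurement.
- The Aim 1 list does not include it.
- In 4.1, a t-test or Mann-Whitney test compares two groups on one variable and has no covariate term.
- In 4.2, a 2-way ANOVA takes two categorical factors. A continuous covariate would make it an analysis of covariance, which is not named.
- Where adjustment is intended, 4.1 says so: regression is specified for neurovascular coupling and for the cognitive measures. For LSCI it specifies only a comparison between groups.

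**Precision.** Let r be the correlation of skin temperature with an LSCI parameter, assumed 0.3 to 0.6. Residual variance after adjustment is 1 − r² of the unadjusted value, and the equivalent sample-size factor is 1/(1 − r²).

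- r = 0.3: 1 − 0.09 = 0.91, so 9% is removed; 1/0.91 = 1.10.
- r = 0.6: 1 − 0.36 = 0.64, so 36% is removed; 1/0.64 = 1.56.

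**Bias.** Let d be the standardised difference in temperature between the groups. With no true COVID-19 effect, the unadjusted difference is b = r × d in SD units. Assume 90 per group, which is 200 less 10% dropout, split equally. The standard error is √(2/90) = 0.149, and the two-sided 5% rejection rate is Φ(b/0.149 − 1.96) + Φ(−b/0.149 − 1.96).

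| r | d = 0 | d = 0.2 | d = 0.5 |
|---|---|---|---|
| 0.2 | b = 0; 5.0% | b = 0.04; 5.8% | b = 0.10; 10.3% |
| 0.4 | b = 0; 5.0% | b = 0.08; 8.4% | b = 0.20; 26.9% |
| 0.6 | b = 0; 5.0% | b = 0.12; 12.7% | b = 0.30; 52.1% |

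The documents give neither r nor d. The first column is the important one: without an imbalance in temperature there is no bias, whatever the correlation.

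**The case against.** The strongest reply is that this is a condensed article. Covariates for a secondary outcome are commonly left to an analysis plan, and 4.1 and 4.2 cover all secondary measures in one line. Table 1 is captioned as a summary for the study aims and omits other recorded items, such as microbleeds and intraocular pressure. The Aim 1 list omits blood pressure too. This stands in part: it cannot be said that temperature will never be used. But the article does name tests for LSCI, and those tests cannot use temperature. The site wording is a measurement instruction that an analysis plan would not correct.

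Several stronger readings are tempting, and the documents do not support them.

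- *The thermometer is certainly at the wrong site.* The mismatch is the plainer reading, not the only one.
- *Thermal vasodilation is being read as endothelial function.* The parameters describe the response after cuff release, and one is relative. The procedure otherwise follows the brachial protocol in 3.2.5, with its 20-minute supine rest. A false group effect needs temperature to differ by COVID-19 status, and no section suggests that it does.
- *Season distorts the visit contrast.* Visits 18 months apart are six months out of phase (18 − 12 = 6). But enrolment runs for about two years (3.7), so with even enrolment the shift averages out of the mean change. It also cancels between groups if they enrol at similar times.
- *Blood pressure should be adjusted for in the same way.* Section 3.2.1 already has it "compared between groups (COVID-19+ and COVID-19-) to assess for differences, which may influence vascular physiological measurements" and excludes uncontrolled hypertension. It is measured after exposure, so adjustment is debatable and nothing there is contradictory.

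One objection bears on the remedy. Finger temperature partly reflects skin blood flow and is also measured after infection, so adjusting for it could remove some of a true effect. That stands, and it is why the unadjusted result should be kept beside the adjusted one.

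**Conclusion.** The concern holds in a limited form. Section 3.2.6 describes the second thermometer site and the second perfusion region inconsistently, and the control for temperature that it announces is not delivered by the analyses named in 4.1 and 4.2. If temperature correlates with the LSCI response, the consequence is lost precision: 9% to 36% of residual variance for an assumed r of 0.3 to 0.6, equivalent to about 10% to 56% more patients for this one endpoint. If r is near zero, the loss is negligible. Bias is conditional on a temperature difference between the groups. The groups are observational and no balancing rule is stated, so a difference is possible, but it is not shown.

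This is a minor point. LSCI is a secondary outcome, and the sample size in 2.4 rests on conversion to dementia. It merits action because the data are already being collected and the remedy serves the protocol's own purpose.

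**What to change.** 1. In 3.2.6, use one description of the two sites for both the temperature reading and the perfusion analysis, after confirming with the operators where the thermometer has actually been placed.
2. Add skin temperature (continuous, before and after LSCI, by region) to Table 1.
3. In 4.1, compare each LSCI measure at Visit 1 by a linear model with COVID-19 status and pre-occlusion skin temperature at the same region. In 4.2, use a mixed model over the two visits with group, visit, their interaction and the pre-occlusion temperature of that visit.
4. Report the unadjusted comparison alongside, and read a marked difference between the two with care, because temperature may lie partly on the path from infection to skin perfusion.
5. For patients already measured, if the second sites prove to differ, rely on the nail bed, where both lists agree.

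The cost is a corrected sentence, one table row and one covariate that is already recorded. The small downside is the possible over-adjustment that step 4 is meant to expose.
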